**Methods/Design:**

This study is a multicenter, prospective, randomized controlled clinical trial (1:1 treatment ratio of fresh vs. elective frozen embryo transfers).. A total of 1,180 infertile PCOS patients undergoing the first cycle of *in vitro* fertilization (IVF) or intracytoplasmic sperm injection will be enrolled and randomized into two parallel groups. Participants in group A will undergo fresh embryo transfer on day 3 after oocyte retrieval, and participants in group B will undergo elective embryo cryopreservation after oocyte retrieval and frozen–thawed embryo transfer in programmed cycles. The primary outcome is the live birth rate. Our study is powered at 80 to detect an absolute difference of 10 at the significance level of 0.01 based on a two-sided test.

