#### *In vitro fertilization and embryo culture*

The oocytes will be inseminated approximately 4 to 6 hours after follicular aspiration. For the scoring of embryos at day 3, we will employ the Puissant *et al.* criteria, with a focus on the number and regularity of blastomeres as well as the percentage fragmentation [20]. Two embryos of top quality will be marked for the first transfer cycle. For patients assigned to group A, two embryos with top quality will be transferred on day 3, and the surplus embryos will been frozen on day 3 or day 5 according to the routine followed at different sites. For patients assigned to group B, all embryos will be cryopreserved and at least two embryos of top quality must be vitrified on day 3. To ensure that two viable, thawed day 3 embryos will be transferred in subsequent programmed cycles, obtaining one or two extra day 3 frozen embryos will be suggested in case frozen embryos lose their viability after thawing.

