#### *Secondary outcomes*

Secondary efficacy parameters will include biochemical pregnancy, clinical pregnancy, implantation rate and ongoing pregnancy. *Biochemical pregnancy* will be defined as a serum β-hCG level ≥10 IU/L 2 weeks after embryo transfer. *Clinical pregnancy* will be defined as the presence of intrauterine gestation sac at 7 weeks gestation. *Ongoing pregnancy* will be defined as a viable pregnancy at 11 weeks gestation. Another secondary outcome will be cumulative live birth results (with each woman having only one allowable live birth) from the single IVF cycle. The safety endpoints will include OHSS, miscarriage, ectopic pregnancy, pregnancy complication, congenital anomalies and neonatal complications.

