### Statistical analysis

#### *Sample size and power calculations*

Investigators in a recent study of Chinese infertile PCOS patients undergoing conventional IVF or ICSI with fresh embryo transfers reported that the live birth rate was 31.2 [21]. Imudia *et al.*, in their cohort study reported a live birth rate of 47.6 in cryothawed embryo transfer cycles [12]. In their randomized trial comparing fresh and frozen–thawed transfer in normal responders (average age = 33 years), Shapiro *et al.* (2011) demonstrated that the clinical pregnancy rate per transfer was 84.0 in the cryopreservation group and 54.7 in the fresh embryo transfer group. They reported that the ongoing pregnancy rates per transfer (at 10 weeks gestation) for these two groups were 78.0 and 50.9, respectively [22]. Shapiro *et al.* also showed that the clinical pregnancy rates per transfer in high responders were 79.6 in the cryopreservation group and 65.4 in the fresh embryo transfer group. They found that the ongoing pregnancy rates were 77.6% in the cryopreservation group and 65.4 in the fresh embryo transfer group [23]. In our present study, we plan to test the primary hypothesis of a difference of 10 in the live birth rate for the two randomization arms. Because all of the participants in this study are under 35 years old, we will assume that frozen–thawed embryo transfer will bring about a live birth rate of 40 and fresh embryo transfer will lead to a live birth rate of 30. A sample size of 530 prospectively enrolled participants in each randomization arm will yield a statistical power of 80 at a significance level of 0.01 to demonstrate an absolute difference in live birth rates of 10 between treatment arms. Taking into consideration a dropout rate of 10 (for example, due to canceled cycles or elective cryopreservation of embryos because of increased risk for OHSS), we will enroll 590 participants into each study group.

For the sample size calculations, the significance level will be set at α = 0.01 and the statistical power will be calculated as 1 - β = 0.80. The live birth rate in group A will be set at 0.30. The live birth rate in group B will set at 0.40. The ratio between groups will be 1:1. The minimum sample size will be 530 for each group, for a total of 1,060 participants. Taking into consideration a dropout rate of 10, we expect to ultimately have a total of 1,180 enrollees, with 590 participants in each group.

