#### *Type of analysis*

We will utilize an intent-to-treat approach to examine differences in the live birth rates for first embryo transfer cycle in the two treatment arms in the primary analysis by the Pearson *χ*^2^ test. Safety parameters and secondary efficacy parameters, such as pregnancy rate, OHSS rate and other rates, will be analyzed using the Pearson *χ*^2^ test and logistic regression (if necessary). Cox proportional hazards models and the Kaplan-Meier method will be applied to compare time to pregnancy and cumulative live birth rates.

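### Implantation rate is naturally counted per embryo, with two embryos planned per woman, but the stated tests treat the embryos as independent

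*Protocol article*

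**What the plan says.** All references are to the protocol article.

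- **Outcomes.** Secondary outcomes: "Secondary efficacy parameters will include biochemical pregnancy, clinical pregnancy, implantation rate and ongoing pregnancy". Clinical pregnancy has its own definition there, the presence of a gestation sac, which gives one result per woman. Implantation rate has no stated numerator or denominator. The safety endpoints in the same section include "pregnancy complication, congenital anomalies and neonatal complications", with no unit stated.
- **Embryos per woman.** In vitro fertilization and embryo culture, for group A: "two embryos with top quality will be transferred on day 3". Embryo transfer and luteal phase support plans two frozen–thawed embryos for group B.
- **Unit of randomisation.** Under Randomization, participants are allocated 1:1, stratified by site.
- **Analysis.** Type of analysis: "Safety parameters and secondary efficacy parameters, such as pregnancy rate, OHSS rate and other rates, will be analyzed using the Pearson" chi-square test and, if necessary, logistic regression. The article mentions no clustering, robust variance, GEE or mixed model.

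**The concern.** The Pearson chi-square and ordinary logistic regression both need independent observations. Two embryos placed in one woman share her endometrium, her hormonal state and the same parents. The trial's own rationale is an effect at that level: the Background proposes that steroid levels just before implantation affect what follows. If that is right, the fates of the two embryos should tend to agree, and a table of embryos holds less information than its count suggests.

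The result would be a p-value that is too small and an interval that is too narrow for a listed efficacy outcome. That outcome bears directly on the proposed mechanism, so an overstated difference could be read as support for the main result.

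**Working it through.** **1. The plan's own figure.** The article gives a sample size only for live birth. Inputs from Sample size and power calculations are 0.30 and 0.40, α = 0.01 and power 0.80. The Abstract adds that the test is two-sided.

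n = [2.576·√(2·0.35·0.65) + 0.842·√(0.30·0.70 + 0.40·0.60)]² / 0.10² ≈ 530 per arm, which matches. Dropout: 530/0.90 = 589, against the stated 590. Live birth is counted once per woman, so nothing below changes these numbers.

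**2. Implantation, two embryos per woman.** The within-woman correlation (ICC) is not in the document and is assumed here.

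- Design effect: DE = 1 + (2 − 1)·ICC = 1 + ICC.
- Understatement of the standard error: 1 − 1/√DE.
- True two-sided error of the naive test: 2·[1 − Φ(z/√DE)], with z = 1.960 (nominal 5%) or 2.576 (nominal 1%).
- Effective number of embryos: 1,060/DE, where 1,060 = 530 women × 2 in one arm.

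| Assumed ICC | DE | SE too small by | Nominal 5% becomes | Nominal 1% becomes | Effective embryos per arm |
|---|---|---|---|---|---|
| 0 | 1.0 | 0% | 5.0% | 1.0% | 1,060 |
| 0.1 | 1.1 | 4.7% | 6.2% | 1.4% | 964 |
| 0.3 | 1.3 | 12.3% | 8.6% | 2.4% | 815 |
| 0.5 | 1.5 | 18.4% | 11.0% | 3.5% | 707 |
| 1 (upper bound) | 2.0 | 29.3% | 16.6% | 6.9% | 530 |

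Example for ICC 0.3: 1.960/√1.3 = 1.719, and 2·[1 − Φ(1.719)] = 0.086.

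**3. Simulation check.** This used 530 women per arm, two embryos each, no true difference, assumed implantation probabilities of 0.25 and 0.35, and 20,000 runs per setting. For ICC 0.1 to 0.5 the naive test at nominal 5% rejected in about 6.2% to 10.9% of runs. A variance computed from woman-level totals gave about 5% and 1% at the two nominal levels. At ICC −0.1 the naive test rejected in 3.8% to 3.9%, so it was conservative.

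**4. Infant outcomes, only if counted per infant.** Only multiple births share a mother. With twin share t among deliveries (assumed), DE = 1 + ICC·2t/(1 + t).

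| Assumed twin share | Assumed ICC | DE | Nominal 5% becomes | Nominal 1% becomes |
|---|---|---|---|---|
| 10% | 0.1 | 1.018 | 5.2% | 1.1% |
| 30% | 0.5 | 1.231 | 7.7% | 2.0% |
| 40% | 0.8 | 1.457 | 10.4% | 3.3% |

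**The case against.** **A condensed article leaves variance estimation to the analysis plan.** This is the strongest objection. A missing sentence on clustering would not be a finding on its own. Here, however, the article does more than stay silent: it assigns a specific test to the secondary rates. Implantation rate is reached through the wording about other rates, since the two rates given as examples, pregnancy and OHSS, are per woman and suit the chi-square. Logistic regression is also named, and a clustered fit is not ruled out, but as written it has no clustering term.

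**Implantation rate is undefined.** This is true, so the embryo denominator is an inference. It is a strong one: a per-woman version would largely duplicate clinical pregnancy, which is listed beside it.

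**The correlation is unknown.** This stands. The document gives neither its size nor its sign. At zero there is no error, and at a negative value the test is conservative.

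**The consequence is limited.** This also stands. The only significance level in the article is the 0.01 used for the primary outcome, and no confirmatory claim is attached to the secondary or safety outcomes.

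A reader might infer that congenital anomalies and neonatal complications are wrongly analysed too, with the same inflation as embryos. The document does not support that. Infant data are recorded at delivery, but the unit of analysis is not stated. Elsewhere the article counts per woman: live birth is any viable infant, and cumulative live birth allows one per woman. Counted that way, the chi-square is valid. Even if these endpoints are counted per infant, two embryos transferred does not mean two infants born, so the embryo figures do not carry over.

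**Conclusion.** The point holds for implantation rate. Following the stated method on embryos gives a standard error that is too small under any positive within-woman correlation. The distortion ranges from modest to material over the assumed ICCs of 0.1 to 0.5. This rests on two assumptions: that the rate is per embryo with two transferred per woman, and that the correlation is positive.

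For the infant safety endpoints the point is conditional on per-infant counting, and the effect there runs from negligible to about double the nominal 5%. The live birth comparison, its sample size, and the secondary outcomes counted once per woman (biochemical, clinical, ongoing pregnancy and cumulative live birth) are not touched. This is a correction that should be made, but it does not threaten the trial's main conclusion.

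**What to change.** 1. Define implantation rate: numerator, denominator, and how women with no transfer or with fewer than two embryos transferred are counted.
2. Analyse it with the woman as the unit (0, 1 or 2 sacs), or by GEE or logistic regression with variance clustered on the woman.
3. State the unit for congenital anomalies and neonatal complications. If it is the infant, use the same clustered method, or report any affected infant per woman.
4. Keep the chi-square for outcomes counted once per woman.

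The cost is a few lines of analysis text and one clustered model. No new data or participants are needed, and Trial status reports recruitment complete with follow-up ongoing. Relative to the naive analysis, intervals for implantation would widen by a factor of √DE: about 1.05 at ICC 0.1, 1.14 at 0.3 and 1.22 at 0.5.

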## Trial status

The study was conceived and designed in 2011. The first participant was randomized in June 2013. We completed recruitment in April 2014, and patient follow-up is ongoing.

## Abbreviations

COH: Controlled ovarian hyperstimulation; E2: Estradiol; FSH: Follicle-stimulating hormone; GnRH: Gonadotropin-releasing hormone; hCG: Human chorionic gonadotropin; ICSI: Intracytoplasmic sperm injection; IVF: *In vitro* fertilization; OHSS: Ovarian hyperstimulation syndrome; PCOS: Polycystic ovarian syndrome; SGA: Small for gestational age.
